### Intervention

Intervention general practices will be supported to implement a new service model incorporating quality incentives for patients’ relational continuity and timely access. The intervention itself will comprise a mechanism of, firstly, patient enrolment within a practice. The practice will then offer enrolled patients: a) guaranteed access to a minimum of three longer appointment types over the study period for older patients or those with chronic or complex illness; b) a review visit within 7 days of admission to an emergency department or hospital, or after other significant health events; and c) for patients aged less than 16 years, same day access for acute conditions.

Figure 2 summarises the incentive structure. All incentives are calculated over the 12 months of the trial and compared with the 12-month period immediately previous to the trial. The incentive payments apply to the percentage of change achieved across the group of enrolled patients at the level of the practice. The incentives supplement the existing payment arrangements. All incentives will be calculated and paid at the conclusion of the 12-month trial.

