### Randomisation of practices

We will use randomisation by minimisation to reduce the risk of the trial being unbalanced across arms by practice size (less than or equal to 5 full-time equivalent GPs, or 6 or more) and Index of Relative Socioeconomic Disadvantage (IRSD) at each practice’s local government area (whether in the most disadvantaged 40% or not, using Socio-Economic Indexes for Areas (SEIFA) [32]. Randomisation will be dynamic and conducted by the trial statistician ([name]) as practice level consent is obtained. The identity of the practices will be masked from the statistician until after the analyses are performed. The project officers in each state will enter a code for each consented practice into a cloud-based database in the order that the practice consents are received and notify the statistician by email. The statistician will then perform dynamic randomisation by minimisation, balancing for practice size and IRSD, entering the allocation into the database. With the exception of the statistician, all participants and project staff will be aware of the practice allocation to the control or intervention arms of the trial.

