**Fig. 2 Fig2:**
[figure not shown]
Plain language incentive structure (as provided to participating general practices)

An intervention facilitator (IF) will be employed by each of the three collaborating centres. They will work with practices in the intervention arm of the study to facilitate implementation of the new service model. They will also collect data relevant to their facilitator role using structured diary keeping. These diaries will contribute data concerning practice culture, communication and routines, plus information about the challenges and successes of the intervention. The EQuIP-GP Trial timeline is summarised in Table 2.

**Table 2 Tab2:** EQuIP-GP Trial timeline

Task Name	Start	Finish
*Practice Recruitment*	April 1 2018	November 30 2018
○ Publicity will be communicated through the PBRN newsletter and/or blog posts		
○ After publicity appears, all practices in the three PBRN’s will be sent a letter, information sheet and consent form.		
○ Practices expressing interest will receive a visit from investigators or a research staff team member to facilitate a more detailed discussion of the study.		
Practice Randomisation ○ Dynamic randomisation of practices will occur after consent has been gained by practices.		
Data collection ○ Distribution of pre-trial provider and facility surveys to practices		
○ A sample of consenting practice staff will be contacted directly by the research team to arrange qualitative interviews following randomisation		
*Patient Recruitment*	June 1 2018	December 31 2018
○ A Practice Nurse in the consenting practices will run an electronic search of the patient database in order to identify potential participants who meet the inclusion criteria		
○ A sample of 200 patients identified in the electronic search will be sent an information pack containing a letter of invitation, an information sheet and a consent form. ○ After 2 weeks, if recruitment is insufficient, then direct invitation to patients presenting to the practice will commence		
Baseline data collection ○ Distribution of pre-trial patient surveys: PCAT, EQ-5D-5 L HRQOL and ease of access survey to parents/guardians of <16 patients.		
○ A sample of consenting patients will be contacted directly by the research team to arrange qualitative interviews following recruitment.		
*Intervention period*	August 1 2018	July 31 2019
Intervention facilitation		
○ Intervention facilitators to visit intervention GP practices 3 times	August 1 2018	January 31 2019

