Follow-up data collection	July 1 2019	August 31 2019
○ A sample of consenting practice staff will be contacted directly by the research team to arrange follow-up qualitative interviews.		
○ Distribution of post-trial patient surveys: PCAT, EQ-5D-5 L and ease of access survey to parents/guardians of <16 patients.		
○ A sample of consenting patients will be contacted directly by the research team to arrange qualitative interviews.		
○ Intervention facilitator interviews		
○ Electronic Health Record data extraction for period August 1 2017 – July 31 2019		

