### Outcomes

The primary outcome of the trial is relational continuity, as measured in the appropriate scale of the 43-item shortened Primary Care Assessment Tool (PCAT) [34]. The domains of accessibility, coordination and comprehensive care in participants will also be measured using the relevant domain scales of the PCAT [34].

We will assess the use of care-related services in the 12 months prior to the trial in comparison with the 12-month trial period. Data elements include:total prescription counts per patient and Pharmaceutical Benefits Scheme (PBS) costs;selected pathology services (microscopy, culture and sensitivity testing for leg ulcer swabs or urine, full blood count, erythrocyte sedimentation rate, thyroid function tests, prostate specific antigen and serum vitamin D level) per patient and Medical Benefits Schedule (MBS) costs;selected radiology services (lower back and chest x-rays, carotid duplex studies, computed tomography of the head) per patient and MBS costs; andtotal specialist referrals per patient and MBS costs.

We will also assess and collect data on hospitalisation and emergency department attendance rates in the 12 months prior to the trial in comparison with the 12-month trial period and for 5 years following the trial. Due to funding and time constraints, it is not possible to adequately power the trial to measure a reduction in PAHs within the study period. Therefore, the study investigators will establish linked data collection procedures to enable ongoing data collection and analysis for up to 5 years. Patient mortality rates will also be assessed for up to 5 years.

The proportion of patients seen within 1 week of discharge from hospital, and under 16-year-olds seen on the same day as requested for acute conditions, will be assessed using quarterly manual chart audits of enrolled patients in each practice performed by the PNs. In addition, patient/parent perceived ease of access will be measured by a brief survey at the beginning and conclusion of the trial, along with health-related quality of life (EQ-5D-5 L) [35]. Table 3 outlines the EQuIP-GP data variables, and Fig. 3 the program logic for the trial.

**Table 3 Tab3:** EQuIP-GP data variables

Data level	Variable	Dependent (DV) or independent variable (IV)	Source
Practice	Locality IRSD	IV	Australian Bureau of Statistics [28]
	Practice size - 6 or more GP FTEs	IV	Practice
	CIHI Practice survey^a^	IV	Practice
GP	CIHI Provider survey^b^	IV	GP

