### Quantitative data analysis

Baseline characteristics will be summarised at the collaborating PBRN centre and general practice levels within each trial arm, to provide counts and frequencies for categorical variables and means with standard deviations or medians and ranges for continuous variables, as appropriate. The primary outcome measure is a between-group difference in changes in the domain of relational continuity, as measured in the appropriate scale of the PCAT [34] at completion of the trial in comparison with baseline. Between-group differences in the domains of accessibility, coordination and comprehensive care in participants will also be measured and tested using the relevant domain scales of the PCAT [34]. To account for the potential effects of clustering, we will use hierarchical linear models with random main effects specified at the general practice level. Total prescription counts for the 12 months prior to trial commencement will also be used to control for case-mix across the trial.

Similarly, each of the other specified outcome variables (Table 2) will be statistically analysed using multi-level modelling methods to test for between-group (intervention vs. control) differences in the change in variables over the course of the study period. It is intended that data collection from administrative datasets (MBS, PBS and hospital admissions) will be continued beyond the trial period for 5 years, and analysed similarly. Data will not be excluded on the basis of non-adherence or protocol violation. The mixed models treat the data as missing at random and incorporate partial datasets, and are appropriate for analysis of datasets with missing data.

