### Trial status

The trial is ongoing, with patient recruitment commencing June 1 2018 and completed December 31 2018 and trial completion July 31 2019. The study was in in the intervention and data collection stages at the time of the protocol manuscript submission.

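### For practices randomised before 1 August 2018, up to a third of the 12-month reference year falls after open allocation, so record-based baselines can depend on arm

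*Protocol article*

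**What the plan says.** **Reference year.** Under Intervention, the article states: "All incentives are calculated over the 12 months of the trial and compared with the 12-month period immediately previous to the trial". Payment follows the percentage change across a practice's enrolled patients. Under Outcomes, service use has the same structure: "We will assess the use of care-related services in the 12 months prior to the trial in comparison with the 12-month trial period". Table 2 gives a single calendar intervention period, 1 August 2018 to 31 July 2019, and lists "Electronic Health Record data extraction for period August 1 2017 – July 31 2019". The reference year is therefore 1 August 2017 to 31 July 2018 for every practice.

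**Randomisation.** Table 2 runs practice recruitment from 1 April 2018 to "November 30 2018" and says: "Dynamic randomisation of practices will occur after consent has been gained by practices". The section Randomisation of practices makes allocation rolling and open. Apart from the statistician, "all participants and project staff will be aware of the practice allocation to the control or intervention arms of the trial".

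**Patients.** They are identified after their practice is randomised. Trial status gives the dates: "The trial is ongoing, with patient recruitment commencing June 1 2018 and completed December 31 2018 and trial completion July 31 2019".

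**Analysis.** Quantitative data analysis tests between-arm differences in change for the service-use outcomes. It adds: "Total prescription counts for the 12 months prior to trial commencement will also be used to control for case-mix across the trial". The Discussion lists fewer radiology and pathology referrals, fewer prescriptions, and fewer avoidable hospitalisations and emergency attendances among the things the incentives are meant to encourage.

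**The concern.** A baseline in a randomised trial should be complete before allocation, so that it cannot depend on arm. Here the reference year is tied to the calendar and not to each practice's randomisation date. Nothing in the article closes it earlier for practices that are randomised before 1 August 2018.

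Three features make this more than a scheduling detail. Allocation is open. Only the intervention arm is paid on change from this year. Several of the rewarded activities are also trial outcomes analysed as change from the same year. An intervention practice that orders more before August raises its baseline and so exaggerates a later reduction. One that adopts the new model early lowers its baseline and so hides part of a real reduction. Control practices have neither reason to shift.

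The outcomes exposed are those taken from records: prescriptions, pathology and imaging, and to a lesser degree hospital and emergency use, over which a practice has less direct control. The prior-year prescription count, used to adjust for case-mix, is exposed in the same way.

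**Working it through.** **Inputs** (Table 2 of the protocol article, all dates inclusive): practice recruitment 1 April to 30 November 2018; patient recruitment from 1 June 2018; intervention period 1 August 2018 to 31 July 2019; EHR window 1 August 2017 to 31 July 2019.

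**1. The plan's own window.** The trial year is 365 days, and the 12 months before it (1 August 2017 to 31 July 2018) are also 365 days. The sum, 730 days, equals the stated EHR window, which confirms the reference year.

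**2. Overlap with open allocation**, by date of randomisation:

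| Randomised on | Reference days after allocation | Share of 365 |
|---|---|---|
| 1 April 2018 (earliest possible) | 122 | 33.4% |
| 15 April | 108 | 29.6% |
| 1 June (patient recruitment opens) | 61 | 16.7% |
| 1 July | 31 | 8.5% |
| 1 August or later | 0 | 0% |

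The recruitment window is 244 days, of which 122 (50%) precede 1 August.

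**3. Size if ordering rises in the overlap.** Let d be the overlap in days and x the assumed relative rise in ordering. The baseline is multiplied by 1 + f, with f = (d/365)x. With no true effect, the apparent change is 1/(1 + f) − 1.

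| x (assumed) | d = 122: baseline shift, apparent change | d = 61: baseline shift, apparent change |
|---|---|---|
| 5% | +1.7%, −1.6% | +0.8%, −0.8% |
| 10% | +3.3%, −3.2% | +1.7%, −1.6% |
| 20% | +6.7%, −6.3% | +3.3%, −3.2% |

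**4. Size if the model starts early.** Suppose the true effect is a 10% fall (assumed) and it is already present for 122 baseline days. The baseline becomes 1 − 0.334 × 0.10 = 0.967 and the trial year 0.90. The observed ratio is 0.90/0.967 = 0.931, an apparent fall of 6.9% instead of 10%.

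**5. Average over an arm.** If consents were spread evenly over the 244 days (assumed), the mean overlap would be (122 × 123/2)/244 = 30.75 days, or 8.4% of the year. With x = 10% in every early intervention practice, f = 0.0084 and the apparent fall is about 0.8%.

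**6. After the change.** A reference year of 1 April 2017 to 31 March 2018 is 365 days with no overlap for any practice. The planned EHR extract starts on 1 August 2017 and so covers 243 of those days; 122 are missing.

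**The case against.** The strongest reply is that the exposure is small and partly hypothetical, and much of that stands.

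- **122 days is a ceiling.** Under Practice recruitment, publicity, a mail-out, phone follow-up and a visit come in stages, so consent on 1 April is unlikely.
- **Targeting starts later.** Payment concerns enrolled patients, who are recruited only from 1 June. Before then a practice could change its care or recording only across the board, so influence aimed at known enrollees has at most 61 days.
- **Many practices may be unaffected.** Those randomised from August have no overlap. The per-practice figures therefore overstate the difference between arms.
- **Knowledge of the payment rule is inferred.** Fig. 2 was given to practices, but the article does not date this. That they knew the terms during the overlap follows reasonably from the information pack and visit before consent, but is not stated.
- **Direction is open.** Inflated ordering and early adoption pull in opposite directions, and the article gives no rate for either.

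A reader might infer more than the article supports:

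- *Longer consultations deferred until August would bias an outcome.* Table 3 codes consultation length as an independent variable, so no listed outcome is affected that way.
- *Post-hospital and same-day access share the fault.* Table 3 takes their prior-year and trial values from patient self-report, and Outcomes assigns the proportions to quarterly chart audits. They are not clearly tied to this record window.
- *The health economic section's claim about perverse incentives is refuted.* That section names cost and effect shifting and cream skimming. It does not claim protection against an open baseline.

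What survives is the structural point: for early practices, part of the reference year follows an allocation that everyone at the practice knows, in an arm paid on change from that year.

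**Conclusion.** The point holds as a limited risk to the record-based secondary outcomes and to the prescription covariate. The overlap follows from the article's own dates: at most 122 days (33%), 61 days (17%) from the opening of patient recruitment, and zero for practices randomised from August. At an assumed 10% rise in ordering, the spurious fall is about 3.2% per practice at the ceiling and about 1.6% at 61 days, and less when averaged over an arm that includes later practices. The behaviour rates are assumptions, and the net direction of bias is unknown.

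It would be tempting to conclude that the primary result is compromised. The article does not support that. Change in PCAT relational continuity is measured from a baseline survey, not from this year of records. The primary model is touched only if the prior-year prescription count enters it as a covariate, and then only through the early practices.

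**What to change.** For the trial analyses of EHR, MBS, PBS and hospital-record outcomes, and for the prescription covariate, define the reference year in both arms as 1 April 2017 to 31 March 2018. Start the extracts on 1 April 2017. Keep the current window (1 August 2017 to 31 July 2018) as a sensitivity analysis; a material difference between the two would itself be informative. Incentive payment terms may stay as issued, since only the analysis window needs to move.

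**Cost.** Extracts begin four months earlier and the protocol or analysis plan wording changes. Table 2 places the EHR extraction in the follow-up phase, July to August 2019, and Trial status describes the trial as ongoing, so the change was still open when the article was written. April to July 2018 then belongs to neither period, and the four-month gap slightly lowers the correlation between baseline and outcome. The window is still a full 12 months, so season stays balanced.

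**Limits.** The change does not recast prior-year items that patients report themselves. Nor does it help practices randomised after 1 August 2018, for which up to 122 days of the fixed trial year (1 August to 30 November) precede allocation. That needs separate treatment.

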**Fig. 2 Fig2:**
[figure not shown]
Plain language incentive structure (as provided to participating general practices)

An intervention facilitator (IF) will be employed by each of the three collaborating centres. They will work with practices in the intervention arm of the study to facilitate implementation of the new service model. They will also collect data relevant to their facilitator role using structured diary keeping. These diaries will contribute data concerning practice culture, communication and routines, plus information about the challenges and successes of the intervention. The EQuIP-GP Trial timeline is summarised in Table 2.

**Table 2 Tab2:** EQuIP-GP Trial timeline

Task Name	Start	Finish
*Practice Recruitment*	April 1 2018	November 30 2018
○ Publicity will be communicated through the PBRN newsletter and/or blog posts		
○ After publicity appears, all practices in the three PBRN’s will be sent a letter, information sheet and consent form.		
○ Practices expressing interest will receive a visit from investigators or a research staff team member to facilitate a more detailed discussion of the study.		
Practice Randomisation ○ Dynamic randomisation of practices will occur after consent has been gained by practices.		
Data collection ○ Distribution of pre-trial provider and facility surveys to practices		
○ A sample of consenting practice staff will be contacted directly by the research team to arrange qualitative interviews following randomisation		
*Patient Recruitment*	June 1 2018	December 31 2018
○ A Practice Nurse in the consenting practices will run an electronic search of the patient database in order to identify potential participants who meet the inclusion criteria		
○ A sample of 200 patients identified in the electronic search will be sent an information pack containing a letter of invitation, an information sheet and a consent form. ○ After 2 weeks, if recruitment is insufficient, then direct invitation to patients presenting to the practice will commence		
Baseline data collection ○ Distribution of pre-trial patient surveys: PCAT, EQ-5D-5 L HRQOL and ease of access survey to parents/guardians of <16 patients.		
○ A sample of consenting patients will be contacted directly by the research team to arrange qualitative interviews following recruitment.		
*Intervention period*	August 1 2018	July 31 2019
Intervention facilitation		
○ Intervention facilitators to visit intervention GP practices 3 times	August 1 2018	January 31 2019
Follow-up data collection	July 1 2019	August 31 2019
○ A sample of consenting practice staff will be contacted directly by the research team to arrange follow-up qualitative interviews.		
○ Distribution of post-trial patient surveys: PCAT, EQ-5D-5 L and ease of access survey to parents/guardians of <16 patients.		
○ A sample of consenting patients will be contacted directly by the research team to arrange qualitative interviews.		
○ Intervention facilitator interviews		
○ Electronic Health Record data extraction for period August 1 2017 – July 31 2019		

### Standard care

Control practices will provide usual care. Usual care in the context of this study is care received by patients in daily practice in regard to their particular health concerns [21], and represents normal practice against which to compare the intervention.

Both intervention and control practices will be provided access to links to quality improvement education materials (e.g. including Choosing Wisely Australia recommendations for improving the quality of healthcare by eliminating unnecessary and sometimes harmful tests, treatments, and procedures [33]).

### Discontinuation criteria

General practices and individual patients can withdraw at any time, without reason. There are no specific discontinuation criteria. Practices and patients can request withdrawal of their data if they discontinue up until the time of analyses. Unless requested by the participant, data will be retained for all participants including withdrawals and deviations from the protocol.

### Outcomes

The primary outcome of the trial is relational continuity, as measured in the appropriate scale of the 43-item shortened Primary Care Assessment Tool (PCAT) [34]. The domains of accessibility, coordination and comprehensive care in participants will also be measured using the relevant domain scales of the PCAT [34].

We will assess the use of care-related services in the 12 months prior to the trial in comparison with the 12-month trial period. Data elements include:total prescription counts per patient and Pharmaceutical Benefits Scheme (PBS) costs;selected pathology services (microscopy, culture and sensitivity testing for leg ulcer swabs or urine, full blood count, erythrocyte sedimentation rate, thyroid function tests, prostate specific antigen and serum vitamin D level) per patient and Medical Benefits Schedule (MBS) costs;selected radiology services (lower back and chest x-rays, carotid duplex studies, computed tomography of the head) per patient and MBS costs; andtotal specialist referrals per patient and MBS costs.

We will also assess and collect data on hospitalisation and emergency department attendance rates in the 12 months prior to the trial in comparison with the 12-month trial period and for 5 years following the trial. Due to funding and time constraints, it is not possible to adequately power the trial to measure a reduction in PAHs within the study period. Therefore, the study investigators will establish linked data collection procedures to enable ongoing data collection and analysis for up to 5 years. Patient mortality rates will also be assessed for up to 5 years.

The proportion of patients seen within 1 week of discharge from hospital, and under 16-year-olds seen on the same day as requested for acute conditions, will be assessed using quarterly manual chart audits of enrolled patients in each practice performed by the PNs. In addition, patient/parent perceived ease of access will be measured by a brief survey at the beginning and conclusion of the trial, along with health-related quality of life (EQ-5D-5 L) [35]. Table 3 outlines the EQuIP-GP data variables, and Fig. 3 the program logic for the trial.

**Table 3 Tab3:** EQuIP-GP data variables

Data level	Variable	Dependent (DV) or independent variable (IV)	Source
Practice	Locality IRSD	IV	Australian Bureau of Statistics [28]
	Practice size - 6 or more GP FTEs	IV	Practice
	CIHI Practice survey^a^	IV	Practice
GP	CIHI Provider survey^b^	IV	GP
Patient	EQ-5D-5 L baseline^c^	IV	Patient self-completion
	EQ-5D-5 L trial completion^c^	DV	Patient self-completion
	PCAT baseline (primary outcome measure)	IV	Patient self-completion [29]
	PCAT trial completion (primary outcome measure)	DV	Patient self-completion [29]
	Hospitalisations previous 12 months (emergency department [ED] + admission)	IV	Patient self-completion
	Hospitalisations during the trial (ED + admission)	DV	Patient self-completion
	Same day consultations <16 years previous 12 months	IV	Patient self-completion
	Same day consultations <16 years during the trial	DV	Patient self-completion
	1 week post-hospital consultations previous 12 months	IV	Patient self-completion
	1 week post-hospital consultations during the trial	DV	Patient self-completion
	DOB	IV	Electronic health record (EHR)
	Sex	IV	EHR
	Smoker	IV	EHR
	Indigenous	IV	EHR
	Diagnoses	IV	EHR
	Medication list number	IV	EHR
	Prescriptions previous 12 months	IV	EHR
	Prescriptions ordered during the trial	DV	EHR
	Pathology received previous 12 months	IV	EHR
	Pathology received during the trial	DV	EHR
	Imaging received previous 12 months	IV	EHR
	Imaging received during the trial	DV	EHR
	Chief diagnoses	IV	EHR
	Time from hospital discharge to appointment	IV	EHR
	Time from request for same day appointment (< 16 yo) to being seen	IV	EHR
	Consultation number	IV	EHR
	Consultation time length	IV	EHR
	Hospitalisations previous 12 months (ED + admission)	IV	EHR
	Hospitalisation during the trial (ED + admission)	DV	EHR
	Mortality during the trial	DV	EHR
	Hospitalisation previous 12 months (ED + admission)	IV	State hospital data
	Hospitalisation during the trial and 5 years following (ED + admission)	DV	State hospital data
	Prescriptions filled previous 12 months	IV	PBS
	Prescriptions filled during the trial and 5 years following	DV	PBS
	Pathology billed previous 12 months	IV	MBS
	Pathology billed during the trial and 5 years following	DV	MBS
	Imaging billed previous 12 months	IV	MBS
	Imaging billed during the trial and 5 years following	DV	MBS
	Specialist consultations previous 12 months	IV	MBS
	Other specialist consultations during the trial and 5 years following	DV	MBS
	Mortality during the trial and 5 years following	DV	Deaths registry

^a^Canadian Institute for Health Information (CIHI). Measuring Organizational Attributes of Primary Health Care Survey. Available at: https://www.cihi.ca/sites/default/files/info_phc_organize_en.pdf [Accessed 8 January 2019]

^b^Canadian Institute for Health Information (CIHI). Attributes of Primary Health Care: Provider Survey. Available at: https://www.cihi.ca/sites/default/files/document/info_phc_provider_en.pdf [Accessed 8 January 2019]

^C^5-level EQ-5D version (EQ-5D-5 L). Available at: https://euroqol.org/eq-5d-instruments/eq-5d-5l-about/ [Accessed 8 January 2019]

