**Methods:**

We will use a mixed methods approach incorporating a two-arm pragmatic cluster randomised control trial with nested qualitative case studies. We aim to recruit 36 general practices from Practice-Based Research Networks (PBRN) covering urban and regional areas of Australia, randomised into intervention and control groups. Control practices will provide usual care while intervention practices will be supported to implement a new service model incorporating incentives for relational continuity and timely access to appointments. Patients will comprise three groups: older (over 65 years); 18–65 years with chronic and/or complex conditions; and those aged less than 16 years with increased risk of hospitalisation. The funding model includes financial incentives to general practitioners (GPs) for providing longer consultations, same day access and timely follow-up after hospitalisation to enrolled patients. The payments are proportional to expected health system savings associated with improved quality of GP care. An outreach facilitator will work with practices to help incorporate the incentive model into usual work. The main outcome measure is relational continuity of care (Primary Care Assessment Tool short-form survey), with secondary outcomes including health-related quality of life and health service use (hospitalisations, emergency presentations, GP and specialist services in the community, medicine prescriptions and targeted pathology and imaging ordering). Outcomes will be initially evaluated over a period of 12 months, with ongoing data collection for 5 years.

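### The two incentivised access measures have conflicting outcome sources, the post-hospital clock is defined two ways, and Table 3 labels the matching EHR rows as independent variables with no period

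*Protocol article*

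**What the plan says.** All references are to the protocol article.

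- **Incentives.** The Abstract (Methods) describes "financial incentives to general practitioners (GPs) for providing longer consultations, same day access and timely follow-up after hospitalisation to enrolled patients". The Intervention section adds: "The incentive payments apply to the percentage of change achieved across the group of enrolled patients at the level of the practice", and "All incentives are calculated over the 12 months of the trial and compared with the 12-month period immediately previous to the trial".
- **Source in the text.** Under Outcomes, the proportion seen within a week of hospital discharge and the proportion of under-16s seen on the day requested "will be assessed using quarterly manual chart audits of enrolled patients in each practice performed by the PNs" (PNs are practice nurses).
- **Source in Table 3.** The row "1 week post-hospital consultations during the trial" and its same-day counterpart for under-16s are dependent variables (DV) from patient self-completion. The EHR row "Time from hospital discharge to appointment" and the EHR time from a same-day request to being seen are independent variables (IV), with no period. Consultation number and "Consultation time length" are also EHR rows marked IV, with no period.
- **Clock.** The Intervention section offers "a review visit within 7 days of admission to an emergency department or hospital", or after other significant health events. Outcomes and the Table 3 EHR row count from discharge.
- **Who handles the data.** Data management has practice staff extracting their practice's own consultation time and access data. Randomisation of practices says that everyone except the statistician knows the allocation.
- **Analysis.** Quantitative data analysis sends the reader to Table 2 for the other outcome variables. Table 2 is the timeline; the variables are in Table 3.

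**The concern.** The second research question under Objectives asks whether the model improves same-day access for children. Post-hospital review is another process the incentive is meant to change. For both measures the article offers three possible sources (nurse audit, self-report, EHR) and does not say which one is the outcome. The sources can disagree, so a result could be chosen after the data are seen.

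The sources also differ in how they can go wrong. The audit is done by staff who know their arm and work in practices that, in one arm only, are paid on improvement in these processes. Error that runs in one direction in one arm does not cancel in the comparison.

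The Table 3 labels add to this. A during-trial value of something the intervention targets is an outcome. Marking it IV without a period leaves it open whether the row is a baseline descriptor, a covariate or a result.

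**Working it through.** The plan gives no figure for these measures, so there is nothing to reproduce. The check sets the sections side by side and then sizes two consequences.

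**1. Sources**

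| Measure | Outcomes text | Table 3, self-completion | Table 3, EHR |
|---|---|---|---|
| Post-hospital review | Nurse chart audit | DV, during trial | IV, no period |
| Same-day access, under 16 | Nurse chart audit | DV, during trial | IV, no period |

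Reading the chart audit as the EHR does not remove the conflict, because the EHR rows are IV and the only DV rows are self-report.

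**2. Labels.** Other EHR measures taken during the trial (prescriptions, pathology, imaging, hospitalisation, mortality) are DV with a stated period. The two EHR timing rows, consultation number and consultation length break that pattern. Longer consultations are incentivised, and the Abstract names GP services in the community among the secondary health service use outcomes. Yet Table 3 has no DV row for consultation length or for GP consultations.

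**3. Clock (post-hospital review only).** For a stay of L days, a seven-day window from admission leaves 7 − L days after discharge:

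- L = 3: 7 − 3 = 4 days
- L = 7: 7 − 7 = 0 days
- L = 10: 7 − 10 = −3, so the window closed three days before discharge

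The discharge window is seven days whatever L is. The same visit can therefore meet one definition and fail the other. Same-day access runs from the request in both Outcomes and Table 3, so its clock is consistent.

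**4. Differential scoring, if the audit is the outcome.** Let p be true attainment, equal in both arms, and f the fraction of true misses scored as met in paid practices only. Recorded attainment is p + f(1 − p) in the intervention arm and p in the control arm, so the false difference is f(1 − p). Neither p nor f is in the document; the ranges are assumptions. Results in percentage points:

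| | f = 0.05 | f = 0.10 | f = 0.20 |
|---|---|---|---|
| p = 0.3 | 3.5 | 7 | 14 |
| p = 0.5 | 2.5 | 5 | 10 |
| p = 0.7 | 1.5 | 3 | 6 |

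The extremes are 0.05 × 0.3 = 0.015 and 0.20 × 0.7 = 0.14.

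**The case against.** Several counter-arguments have force.

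- **Audit bias and Table 3 do not operate together.** If Table 3 governs, the outcome is patient self-report and audit scoring does not touch it. This stands, and the bias above is conditional on the Outcomes text governing. It does not settle which one governs.
- **The payment link is partly inferred.** The article does not say that the nurse audit supplies the payment data, and the payment detail is in Figure 2, which is not shown. This stands. What is stated is that these processes are incentivised, that payment follows practice-level change, and that the auditors are unblinded practice staff. No independent check is described.
- **Other evidence on access exists.** There is a perceived ease-of-access survey and the accessibility domain of the Primary Care Assessment Tool (PCAT). The access question therefore does not rest on these measures alone.
- **Table 3 is a list of data variables, not a model specification.** A reader might infer from the IV labels that during-trial consultation length and time to appointment will be adjusted for, removing part of the intervention effect and cutting power for the primary outcome. The document does not support that. Quantitative data analysis names one added covariate, prescription counts from the 12 months before the trial, and nowhere says that every IV enters a model.
- **GP services are named as an outcome.** A reader might infer from Table 3 that consultation measures are outcomes nowhere in the article. The Abstract shows otherwise; the gap is in Table 3.

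**Conclusion.** The point holds as an internal contradiction that should be settled before analysis. The outcome source for both access measures differs between the Outcomes text and Table 3. Four EHR rows on processes the intervention acts on are marked IV without a period. The post-hospital clock runs from admission in one section and from discharge in two other places. The pointer to Table 2, which should lead to the outcome list, leads to the timeline.

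The possible size is 1.5 to 14 percentage points of false difference. That rests on three assumptions: the audit is the outcome source, true attainment is 30–70% in both arms, and 5–20% of misses are scored as met in paid practices only. It illustrates the exposure and is not evidence that such scoring would occur. The primary outcome, patient-completed PCAT relational continuity, does not depend on the audit. No loss of power for it is claimed, because adjustment for during-trial process values is not a stated step.

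**What to change.** 1. Name one outcome source for each of the two measures, the same in both arms. The preferred choice is central derivation by one algorithm, blind to arm, from the planned EHR extract, with state hospital dates where linkage consent exists. Treat the nurse audit and self-report as supportive. State as a limitation that EHR recording still lies with the practices.
2. In Table 3, split the two EHR timing rows, consultation number and consultation length into previous-12-months (IV) and during-trial (DV) rows. Table 2 plans EHR extraction from August 2017 to July 2019, which spans both periods. State that only pre-allocation values may be covariates.
3. In Quantitative data analysis, change the reference for the outcome variables from Table 2 to Table 3.
4. Reconcile the admission wording under Intervention with the discharge wording under Outcomes and in Table 3. Which is right is for the investigators to say.

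The cost is wording and a little programming on an extract already planned. Linked hospital dates arrive later than the audit and only for patients who gave express consent. Medicare claims should not be assumed as a source of GP consultation dates, because the Medicare rows in Table 3 cover pathology, imaging and specialist consultations only. The trial was in its intervention and data collection stages when the article was submitted, but all four changes can be made before the analysis.
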